### 11d. Adverse Events

*Adverse Event (AE)*: is any untoward medical occurrence in a patient or clinical study subject.

*Serious Adverse Event (SAE)*: any untoward and unexpected medical occurrence or effect that:

- Results in death
- Is life-threatening – refers to an event in which the subject was at risk of death at the time of the event; it does not refer to an event which hypothetically might have caused death if it were more severe
- Requires hospitalisation, or prolongation of existing inpatients' hospitalisation
- Results in persistent or significant disability or incapacity
- Is a congenital anomaly or birth defect

Medical judgement should be exercised in deciding whether an AE is serious in other situations. Important AEs that are not immediately life-threatening or do not result in death or hospitalisation but may jeopardise the subject or may require intervention to prevent one of the other outcomes listed in the definition above, should also be considered serious.

#### *Reporting Procedures:*

All adverse events should be reported. Depending on the nature of the event the reporting procedures below should be followed. Any questions concerning adverse event reporting should be directed to the Chief Investigator in the first instance.

#### *Non serious AEs*

All such events, whether expected or not, should be recorded- it should be specified if only some non-serious AEs will be recorded, any reporting should be consistent with the purpose of the trial end points.

#### *Serious AEs*

An SAE form should be completed and emailed to the Chief Investigator within 24 hours. However, relapse and death due to and hospitalisations for elective treatment of a pre-existing condition do not need reporting as SAEs.

All SAEs should be reported where in the opinion of the Chief Investigator, the event was:

- 'related', ie resulted from the administration of any of the research procedures; and
- 'unexpected', ie an event that is not listed in the protocol as an expected occurrence

Reports of related and unexpected SAEs should be submitted within 15 days of the Chief Investigator becoming aware of the event, using the NRES SAE form for non-IMP studies. The Chief Investigator must also notify the Sponsor of all related and unexpected SAEs.

Local investigators should report any SAEs as required by their Local Research Ethics Committee, Sponsor and/or Research & Development Office.

Contact details for reporting SAEs:

[[contact]](mailto:[contact])

Chief Investigator: [[contact]](mailto:[contact])

## 12. Ethical Considerations

### **ETHICS APPROVAL**

The Study Coordination Centre has obtained approval from the Ministry of Defence Research Ethics Committee (MODREC) and Health Regulator Authority (HRA). The study must also receive confirmation of capacity and capability from each participating organisation before accepting participants into the study or any research activity is carried out. The study will be conducted in accordance with the recommendations for physicians involved in research on human subjects adopted by the 18th World Medical Assembly, Helsinki 1964 and later revisions.

### **CONSENT AND CONFIDENTIALITY**

Individual informed consent for the capture, storage and analysis of HoloLens™ MR data and scenario recordings will be obtained from all participants as required. It will be the responsibility of local collaborators to obtain written informed consent from each participant after adequate explanation of the project, potential hazards and process for data capture and storage. The original copy of the signed and dated informed consent must be retained at the participating organisation and is subject to inspection by representatives of the Sponsor, or representatives from Regulatory Authorities. The standardised information sheet and consent form is included in this protocol. The Chief Investigator will preserve the confidentiality of participants taking part in the study and is registered under the Data Protection Act.

### **INDEMNITY**

Imperial College London holds negligent harm and non-negligent harm insurance policies which apply to this study.

### **SPONSOR**

Imperial College London will act as the main sponsor for this study

### **DATA STORAGE AND RETENTION**

All data will be stored for a minimum of 10 years (or according to changes in regulatory requirements). Data generated by this work will be processed in accordance with the Data Protection Act 2018. Retention and analysis will be conducted with regard to all local policies relating to the collection, holding and disclosure of data relating to individuals. The Principal and Co-applicants will act as custodians of the data and be responsible for its security. The CI will ensure the continued storage of all relevant data and documentation, even if they leave the clinic/practice or retire before the end of the required storage period. Delegation will be documented in writing.

### **AUDITS**

The study may be subject to inspection and audit by Imperial College London under their remit as sponsor and other regulatory bodies to ensure adherence to GCP and the UK Policy Framework for Health and Social Care Research.

### 13. Participants

**13a. Number of Participants:** 30

**13b. Lower Age Limit:** 18

**13c. Upper Age Limit:** No restrictions

**13d. Birth Sex (male/female):** No restrictions.

**13e. Please provide justification for the sample size, and age/sex restrictions:** It is not possible to perform a power calculation for this work, as there are currently no data available on HL2 interventions upon which a standard deviation of the primary outcome measure can be calculated. The objective of this pilot study is therefore to determine a power calculation for a formal randomised control trial in patients.

### 14. Selection Criteria

**14a. List your participant inclusion criteria:**

Clinical staff who provide care to COVID-19 patients at Imperial College Healthcare NHS Trust and Imperial College London. This will include doctors in training and equivalent non-training grade medical staff, in addition to independent specialist nurse practitioners. All participants will have prior experience/qualifications in advanced life support skills and resuscitation. Subjects should be 18 or above.

**14b. List your participant exclusion criteria:**

Those already independently competent in advanced airway management  
Unable to consent  
Unable to wear MR headset – either because of head shape or because of problems with nausea or previous challenges with VR.  
Unwilling or unable to take part

### 15. Recruitment

**15a. Describe how potential participants will be identified:**

The study is being undertaken at a single institution. Potential participants will be individuals who have already undertaken a simulation programme in life support skills at the Trust or College. They will be identified through the Medical Education Department at Imperial College Healthcare NHS Trust who already have an established program of simulation training, including a specific focus on COVID-19 preparation and resilience building. This process will be undertaken in conjunction with the Director of Medical Education. The organisation has an established track record of providing simulation training in addition to the evaluation of these educational programs; standard local practices for conducting such work will be followed throughout the conduct of this study.

**15b. Describe how potential participants will be approached:**

They will be approached via the Medical Education Department or Simulation Team from Imperial College Healthcare NHS Trust / Imperial College. Participants will also be approached at hospital educational events. Example wording for the content of

recruitment material is provided in Appendix 2; all final materials will be subject to local Trust and College approval at the time of recruitment.

**15c. Describe how potential participants will be recruited:**

Participants will email the CI if they wish to be involved. They will then be sent information sheets and the consent form. If they are still interested, they will then be able to contact and speak to the CI and be given a verbal briefing.

**16. Consent**

**16a. Describe the process you will use when seeking and obtaining consent:**

Consent to enter the study must be sought from each participant only after a full explanation has been given, an information leaflet offered, and time allowed for consideration. All participants will receive a participant information sheet, and consent form. They will have an opportunity to read the PIS and consent form for at least 24 hours prior to attending the simulation event, where a researcher will answer any questions before inviting them to complete the consent form. Signed consent will be obtained from all participants. All participants are free to withdraw at any time from the study without giving reasons and without prejudice.

**16b. Do you plan to include participants who are children (under 16 yrs)?**

No

**16c. Do you plan to include participants who are aged 16 or 17?**

No

**16d. Do you plan to include participants who lack capacity to consent?**

No

**16e. Do you plan to include any prisoners? No**

**16f. Are there special pressures that might make it difficult for people to refuse to take part in the study (e.g. subordinates)?**

No. Junior doctors working under one of the study team may feel pressure to take part, however, this is not foreseen to be a significant risk as this potential conflict is managed on a regular basis within the Trust and College through established pathways. In addition, the NHS and its staff remain under pressure due to the ongoing demands of responding to the pandemic. Asking staff to devote further time to participating in this study may therefore create an additional burden. We will seek to address this by explaining the potential benefits of the technology - in reducing the stress/demands of caring for patients during the pandemic - in order for participants to feel they are directly contributing to direct improvements in the working lives of staff and care delivered to patients. In addition, we will ensure participants undertake the study at a manageable point during their standard working week, as is currently the case with all medical simulation/education, so the study does not take away important periods of rest and relaxation for participants to ensure that their physical and mental well-being is protected.

If any Junior Doctor feels pressure to take part, they will be encouraged to report this through the Medical Education Department or Freedom to Speak Up Guardian at the Trust.

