#### Outcome measures:

The primary outcome will be

- Error rate as assessed by the validated ICECAP Tool (Imperial College Error Capture Tool) a validated multi-dimensional assessment of error

Secondary outcomes will be

- Time to complete the clinical scenario
- Successful completion of the clinical scenario - as assessed by simulation team
- Global assessment of team performance - assessed using the validated OTAS Tool (Observational Teamwork Assessment for Surgery) and T-SAW-C Tool (Teamwork Skills Assessment for Ward Care)
- Errors in PPE use - assessed according to Public Health England (PHE) guidance and number of visor failures (e.g., inadvertent removal, misting, contamination or obstruction of clinical care)
- Participant stress/cognitive load - assessed via the validated NASA Task Load Index (NASA-TLX) and State Trait Anxiety Index (STAI) Tools
- Usability / technology feedback questionnaire for those wearing the HL2

All questionnaire items and assessment tools listed above are provided in the attached documents. Participant responses will be collected at the time of study completion, and assessment of video recordings will be undertaken during the data analysis stage of the study

**Statistical analysis:** Standard descriptive data will be employed. Independent two-sample t-tests will be calculated for normal continuous data, including ICECAP and OTAS scores, and time-to completion data. The Wilcoxon-Mann-Whitney U test will be used to analyse TLX scores. Multivariate linear regressions will be calculated to control for potential confounders and to assess association. Within subject comparisons will also be made to assess how the technology influences individual performance.

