## **Appendix 2 - example wording for recruitment e-mails / materials**

Dear Colleagues,

COVID-19 has brought many challenges to how we can deliver the highest quality care to our patients whilst keeping our staff safe.

As you know, in the first wave of COVID-19 the Trust and Imperial College used the HoloLens device in a limited way to support the provision of remote care for our patients. This work showed that this new technology may help improve the quality of care we provide to patients and reduce the risk to staff from COVID-19.

The team who led this work has now been funded by the Ministry of Defence to further assess the effectiveness of the HoloLens headset, and to better understand how it can improve communication and teamwork, and reduce stress and risk for staff. This work is being undertaken in conjunction with the Medical Education Department and Simulation Team at St Mary's Hospital in support of our COVID-19 response locally.

We would like to invite you to volunteer to take part in a simulated trial of using the HoloLens device to help you assess and treat patients with COVID-19. The trial will take place over half a day in the simulation lab at St Mary's, and will involve teaching you how to use the technology, providing revision on the assessment and resuscitation of the critically unwell patient and undertaking two simulated patient scenarios.

If you would like more information, or would like to take part then please contact the simulation team - (email / telephone contact tbc).

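### Recruitment wording that the headset may reduce stress and improve care creates an avoidable risk of expectation bias in the unmasked self-ratings of stress and workload

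*Protocol*

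**What the plan says.** Section 16f asks about pressures on prospective participants. To address the extra burden on staff, it proposes "explaining the potential benefits of the technology - in reducing the stress/demands of caring for patients during the pandemic", and gives the purpose as "in order for participants to feel they are directly contributing to direct improvements in the working lives of staff and care delivered to patients". It also says the study will be scheduled at a manageable point in the normal working week.

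Appendix 2 gives example recruitment wording. It says of the earlier local use of the device that "this new technology may help improve the quality of care we provide to patients and reduce the risk to staff from COVID-19", and describes the new study as intended "to better understand how it can improve communication and teamwork, and reduce stress and risk for staff".

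Section 10, under Outcome measures, lists among the secondary outcomes "Participant stress/cognitive load - assessed via the validated NASA Task Load Index (NASA-TLX) and State Trait Anxiety Index (STAI) Tools" and "Usability / technology feedback questionnaire for those wearing the HL2". Participant responses are collected at study completion. The primary outcome is the ICECAP error rate. Teamwork is scored with OTAS and T-SAW-C, and the simulation team judges completion. Scenarios are video recorded and assessed by two independent researchers.

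The hypothesis in section 10 is that HL2-supported care is equivalent to standard practice for team performance, workload and technical performance. Section 9 says that robust trial evidence is lacking.

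**The concern.** Someone wearing a headset knows it, so participants cannot be masked. For outcomes that they rate themselves, one of the few available protections is to avoid suggesting in advance what the answer might be. Here the recruitment material names stress, which participants later score in both conditions. In a cross-over, each person contributes both ratings, so an expectation attached to the headset acts directly on the HL2-versus-standard contrast.

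A shift in the headset's favour could produce an apparent reduction in stress. It could also hide a real increase in workload, which matters because the hypothesis claims equivalence on workload. No later analysis can separate a suggested effect from a real one.

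**Working it through.** **The text, link by link**

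1. *Message.* Section 16f offers potential stress reduction as a reason to take part. Appendix 2 asks how the device can reduce stress, not whether it does.
2. *Same construct, self-rated.* Stress and cognitive load are measured by NASA-TLX and STAI, after recruitment and after both scenarios.
3. *No masking.* Section 10 (Group 2) has the participant wear the headset.
4. *The study's own position.* The hypothesis is equivalence, with workload named. Section 9 describes the earlier evaluation as reducing potential COVID-19 contacts by 80% and lowering PPE consumption. It reports no result on stress or quality of care, yet the e-mail says "This work showed that this new technology may help improve the quality of care we provide to patients".

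**Which outcomes are exposed**

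| Outcome | Self-reported? | What could shift |
|---|---|---|
| NASA-TLX, STAI | Yes, both conditions | The HL2-versus-standard difference |
| Usability questionnaire | Yes, HL2 only | The absolute level; there is no comparator |
| OTAS, T-SAW-C, completion | No | Not through self-report |
| ICECAP (primary) | No | Not through self-report |

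**Illustration of size**

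The protocol states no SD, margin, alpha or power (section 13e), so there is no figure to reproduce. Only n = 30 comes from the document. Assumed: a paired t-test, two-sided alpha 0.05, within-person correlation ρ of 0.3 to 0.7, and an expectation shift b in SDs of the outcome. The paired form corresponds to the within-subject comparisons in section 10. The unpaired tests also named there would give different figures.

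- SD of the paired difference = √(2(1 − ρ)) outcome SDs: 1.183 at ρ = 0.3, 1.000 at 0.5, 0.775 at 0.7.
- Noncentrality = b × √30 / √(2(1 − ρ)). For b = 0.2 and ρ = 0.5 this is 0.2 × 5.477 / 1 = 1.095, and the noncentral t on 29 degrees of freedom gives a rejection probability of 0.185.

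Probability of a significant result when there is no true difference:

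| Shift b (SD) | ρ = 0.3 | ρ = 0.5 | ρ = 0.7 |
|---|---|---|---|
| 0 | 0.050 | 0.050 | 0.050 |
| 0.1 | 0.073 | 0.083 | 0.105 |
| 0.2 | 0.146 | 0.185 | 0.277 |
| 0.3 | 0.269 | 0.355 | 0.536 |
| 0.5 | 0.609 | 0.754 | 0.927 |

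The test is two-sided, so an unfavourable shift of the same size gives the same rates.

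*Masking.* Suppose HL2 truly raised workload by 0.5 SD (ρ = 0.5). Power to see it is 0.754 without bias. A favourable shift of 0.2 SD leaves an apparent 0.3 SD and power of 0.355. A shift of 0.3 SD leaves 0.2 SD and power of 0.185.

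*Scale.* The half-width of a 90% interval for a paired difference is t(0.95, 29)/√30 = 1.699/5.477 = 0.310 SDs of the difference. In outcome SDs that is 0.310 × 1.183 = 0.37 at ρ = 0.3, 0.31 at ρ = 0.5, and 0.310 × 0.775 = 0.24 at ρ = 0.7. Whether a shift of 0.2 to 0.3 SD is comparable with the precision of the study therefore depends on a correlation that the protocol does not give.

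**The case against.** A reader might infer that participants are told the headset does reduce stress and improve care. The text does not go that far: section 16f says potential and Appendix 2 says may. A reader might also infer that all the promoted benefits are then self-rated. They are not. Of stress, communication, teamwork and quality of care, only stress is rated by the participant.

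The construct match is also looser than it first appears. Section 16f speaks of the stress of caring for patients in the pandemic, while NASA-TLX and STAI are used for stress and load in the study. The answer addresses an ethics question and is not a session script.

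What participants finally read is not fully visible. Appendix 2 is example wording subject to local approval (section 15b), and recruitment also takes place at educational events, so not everyone need receive the e-mail. Every participant receives an information sheet at least 24 hours before attending (section 16a), and section 15c describes a verbal briefing. The sheet is not among the pages available here and may be balanced. The protocol itself mentions discomfort and disorientation (17a) and no direct benefit (17h).

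Finally, neither the direction nor the size of a shift is established. High expectations of an unfamiliar headset could end in disappointment. Neutral wording is not a full remedy, since participants must be told the purpose and will know the condition.

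All of this stands and limits the point. It does not remove it: Appendix 2 refers to reducing staff stress in general terms, 16f commits the team to a stress-benefit message, and stress is then self-reported unmasked.

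**Conclusion.** The point holds as an avoidable risk of expectation bias in two secondary outcomes, NASA-TLX and STAI, and in the absolute level of the HL2 usability ratings. Its size and direction are unknown. If the shift were 0.1 to 0.3 SD, the false-positive rate of a nominal 5% paired comparison would lie between 7% and 54% over correlations of 0.3 to 0.7. These figures rest on assumed shifts, correlations and alpha, and are not estimates of what will happen.

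The documents do not support a claim that the primary outcome is compromised through self-report, that ratings will necessarily favour HL2, or that participants receive no balanced information. For a 30-person pilot whose stated objective is to inform a later power calculation, this is a low-cost improvement and not a flaw that undermines the study. It is worth making now because it cannot be corrected at analysis.

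**What to change.** - **Section 16f:** replace the stress-reduction message with a statement that it is not known whether the device makes care easier, harder or no different. Rely on the scheduling measure already in 16f to address burden.
- **Appendix 2:** replace the wording on improved quality of care, communication, teamwork and reduced stress with *to compare working with and without the HoloLens*. The statement on reduced staff risk may stay if it is limited to exposure, because section 9 reports fewer potential contacts in the earlier evaluation.
- **Information sheet and session briefing:** check them against the same neutral wording so that all materials agree.

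The cost is a change to one protocol paragraph and to an example e-mail whose final form still awaits local approval. The downside is possibly slightly less persuasive recruitment. Participants will still know which condition they are in, so the self-reported outcomes should be read with that limitation.

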**17. Participant Involvement: Risks, Requirements and Benefits**

**17a. Describe potential hazards, risks or adverse effects that may be associated with the study?**

The work will be performed within a simulated environment, where the risks to staff members are minimised. The major risk comes through the potential for COVID-19 transmission as described in section 11.

There is the possibility that a subject may feel uncomfortable or disorientated whilst wearing the HL2 device. If this occurs, then they will have the opportunity to stop the simulation and then either recover and carry on or withdraw from the study. Members of the simulation faculty and study team will be present throughout, and if there is any sign that subject are at risk of injury from becoming disorientated whilst wearing the device they will step in to stop the simulation and support the participant to prevent injury.

